### Data analysis

Descriptive and inferential statistical analyses will be conducted using IBM SPSS-Amos software. The Kolmogorov-Smirnov test will be correspondingly applied to check the normality of the data. If the data are normally distributed then t-tests, paired-samples t-tests, and analysis of variance (ANOVA) will be operated as needed. Analysis of covariance (ANCOVA) will be employed to investigate the difference in the mean scores of the experimental and control groups in terms of the study variables at the pre- and post-intervention stages. If the data are not normally distributed, non-parametric analysis will be used. In this case, the Mann-Whitney U test will be used to compare two groups before and after the intervention, and the Wilcoxon signed-rank test will be applied to compare each group at the pre- and post-intervention stages, and the Kruskal–Wallis test will be exploited for the between- and within-group comparisons.

In addition, structural equation modeling will be utilized to analyze and evaluate the fit of the model.

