## Methods

### Study design, setting and participants

This quasi-experimental study is a non-blinded randomized controlled trial (RCT) (Code: IRCT20220509054790N1) with assessments at baseline, immediately after the intervention, and three months after the intervention. This study was approved by the Ethics Committee in Medical Research affiliated to Shiraz University of Medical Sciences, Shiraz, Iran.

Recruitment will be from two large healthcare centers in the northern and southern parts of the city of Shiraz, in southern Iran (namely, Wal-fajr and Enghelab). Permission to undertake the study in these two healthcare centers was sought as they are comparable in their cultural and socio-economic characteristics. This method has previously been used as a means of preventing information exchange between the participants in the experimental and control groups [53]. The two healthcare centers will be randomly assigned to intervention and control settings following recruitment. Using the MedCalc software and the following formula:$$n \ge \frac{{(Z_{{1 - {\raise0.5ex\hbox{$\scriptstyle a$} \kern-0.1em/\kern-0.15em \lower0.25ex\hbox{$\scriptstyle 2$}}}} + Z_{{1 - \beta }} )\left( {\sigma _{1}^{2} + \sigma _{2}^{2} /r} \right)}}{{(\mu _{1} - \mu _{2} )^{2} }}$$

The sample size is estimated to be 66 participants in each group. Considering the 5% loss of observations, the final sample size will be determined to be 69 in each group.

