### Data collection and instruments

Data will be collected at three time points from both the intervention group and the control group. A pen and paper survey will be distributed at dedicated times during the working day, according to HCW shift. Time will be set aside for participants to complete their survey, and post anonymously in a sealed collection box. made up for the following instruments:

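### The non-normal branch applies Kruskal-Wallis to repeated measures on the same people, and as naturally read it drops baseline adjustment from the group comparison

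*Protocol article*

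**What the plan says.** All points are in the protocol article.

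- **Design.** Under Study design, setting and participants there are two groups, one healthcare center each, with "assessments at baseline, immediately after the intervention, and three months after the intervention". Data collection and instruments confirms: "Data will be collected at three time points from both the intervention group and the control group". The sample size is 66 per group before loss and 69 after.
- **Hypothesis.** The first item under Research hypotheses concerns a difference between the groups in mean change scores.
- **Gate.** Under Data analysis, "The Kolmogorov-Smirnov test will be correspondingly applied to check the normality of the data". The section then states: "If the data are not normally distributed, non-parametric analysis will be used".
- **Normal branch.** t-tests, paired t-tests and ANOVA are listed, followed by "Analysis of covariance (ANCOVA) will be employed to investigate the difference in the mean scores of the experimental and control groups" at the pre- and post-intervention stages.
- **Non-normal branch.** Three tests are named. The group comparison is covered first: "the Mann-Whitney U test will be used to compare two groups before and after the intervention". A paired test then serves for change between two stages: "the Wilcoxon signed-rank test will be applied to compare each group at the pre- and post-intervention stages". The last clause gives an independent-samples test a double role: "the Kruskal–Wallis test will be exploited for the between- and within-group comparisons". No Friedman test, rank ANCOVA or other baseline-adjusted method appears in this branch.

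**The concern.** Kruskal-Wallis compares independent samples. Three surveys from the same people are not independent, so its reference distribution is wrong for a within-group comparison over time. The plan is also inconsistent about pairing, since the same sentence uses the paired Wilcoxon test for two stages. Between two groups Kruskal-Wallis is equivalent to Mann-Whitney and adds nothing, so no reading gives the clause a useful role.

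The second matter is the group effect. ANCOVA is the only baseline-adjusted analysis named. If normality is rejected, the natural reading is that Mann-Whitney before and after takes its place. That discards baseline information already collected and does not address the stated change hypothesis. Several questionnaire totals will be tested, so one outcome could be baseline-adjusted and the next not, depending on a preliminary test. With one center per arm a baseline difference is plausible, and an unadjusted comparison of follow-up scores would carry it forward as an apparent effect.

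**Working it through.** The plan gives no figure on this point to reproduce. The only input taken from it is n = 66 per group. Assumed, because the article does not give them: within-person correlation ρ, effect sizes in SD units, and the size of any baseline gap between centers. Tests are two-sided at 5%. Simulations used normal scores unless stated, with 20,000 replicates for the main runs.

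**1. Kruskal-Wallis within one group, three time points.**
With equal correlation between waves, the statistic under no change behaves approximately as (1 − ρs) times a chi-square on 2 degrees of freedom. Here ρs = (6/π)·arcsin(ρ/2) is the rank correlation. The true size is therefore about 0.05^(1/(1 − ρs)).
- ρ = 0.3: ρs = 0.288, size ≈ 0.05^(1/0.712) = 1.5%
- ρ = 0.5: ρs = 0.483, size ≈ 0.05^(1/0.517) = 0.31%
- ρ = 0.7: ρs = 0.683, size ≈ 0.05^(1/0.317) = 0.008%

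Simulation agrees. The power columns are for a 0.3 SD shift at both follow-ups.

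| ρ | Size: Kruskal-Wallis | Size: Friedman | Power: Kruskal-Wallis | Power: Friedman |
|---|---|---|---|---|
| 0.3 | 1.4% | 4.8% | 34% | 40% |
| 0.5 | 0.28% | 4.9% | 29% | 55% |
| 0.7 | 0.01% | 4.8% | 23% | 78% |

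At ρ = 0 Kruskal-Wallis holds 5%, so the ignored pairing is the cause. Repeat runs with other seeds moved the size at ρ = 0.5 between about 0.2% and 0.4%.

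**2. Group effect, no baseline gap, true effect 0.4 SD, normal data, ρ = 0.6 to 0.7.**
The ANCOVA signal is 0.4/√(1 − ρ²) × √(66/2). At ρ = 0.6 this is 0.5 × 5.745 = 2.87, and Φ(2.87 − 1.96) ≈ 82%. At ρ = 0.7 it is 0.560 × 5.745 = 3.22, giving about 90%. Simulated power:
- Mann-Whitney on follow-up scores: 60% to 61%
- ANCOVA: about 81% to 89%
- rank ANCOVA: about 78% to 87%

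**3. False positives from a baseline gap between centers, no intervention effect, ρ = 0.6 to 0.7.**

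*If the gap shrinks to ρ times its baseline size by follow-up.* For a 0.3 SD gap, Mann-Whitney rejects in about 17% to 22% of trials and ANCOVA in about 5%.

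*If the gap stays the same size.* ANCOVA keeps a bias of gap × (1 − ρ). For 0.3 SD and ρ = 0.6, the signal is 0.3 × 0.4/0.8 × 5.745 = 0.86, which gives about 14% rejections. Mann-Whitney's signal is about 0.3 × 5.745 × √(3/π) = 1.68, which gives about 39%. Simulated:

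| Stable gap | Mann-Whitney | ANCOVA, ρ = 0.6 | ANCOVA, ρ = 0.7 |
|---|---|---|---|
| 0.3 SD | about 38% to 39% | 13% to 14% | 11% |
| 0.5 SD | about 79% | 28% | 21% |

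Adjustment is better under both assumptions, but it is protective at 5% only under the first. A lower ρ leaves more bias: at ρ = 0.5 ANCOVA rejects in 16% (0.3 SD) and 36% (0.5 SD) of trials.

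**The case against.** **The Kruskal-Wallis error is conservative and secondary.** This stands. Effectiveness is a between-group question, and a within-group test cannot establish it. The cost is lost power in a supporting comparison, not false claims. The rule is still wrong as written.

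**ANCOVA may be unconditional.** Its sentence is not grammatically tied to the normality condition. But the text that follows introduces Mann-Whitney as what is done in the non-normal case, so the branch reading is the more natural one. The Kruskal-Wallis error stands on either reading.

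**The power comparison uses normal data, which would not usually trigger this branch.** This also stands. With lognormal scores and the same 0.4 SD shift on the log scale, Mann-Whitney against raw-scale ANCOVA gave 61% against 46% (ρ = 0.3), 60% against 50% (0.5), 61% against 57% (0.6) and 61% against 64% (0.7). Lognormal is an extreme case. Rank ANCOVA depends only on ranks, so its advantage over Mann-Whitney is unchanged. The argument is for adjustment, not for raw-scale ANCOVA regardless of shape.

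**Two stronger readings are tempting but not supported.** A reader might infer that the normality test is run on raw scores; the text refers only to the data, and such detail may sit in an analysis plan that is not shown. A reader might also infer that the three-month survey has no adjusted comparison; the abstract counts both follow-ups among its three stages, so the plural post-intervention stages can cover three months.

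**Perhaps independent-samples tests were chosen because surveys are posted anonymously.** That does not fit, because paired t-tests, the Wilcoxon test and ANCOVA all need linked records.

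**Conclusion.** The concern holds in limited form. Kruskal-Wallis is the wrong test for within-group comparisons here. With ρ assumed at 0.5 to 0.7, its size is about 0.3% or less, and its power for a 0.3 SD shift falls to about 29% to 23%, against 55% to 78% for Friedman.

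On its natural reading the same branch also makes baseline adjustment depend on a Kolmogorov-Smirnov result and leaves the change hypothesis untested. Mann-Whitney is inferior here, not invalid in itself: with no baseline gap it keeps its 5% level in the simulations. For a 0.4 SD effect in normal data it has 60% to 61% power, against about 78% to 87% for rank ANCOVA.

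It would be tempting to say that ANCOVA removes the bias from non-equivalent centers. The documents do not support that, because nothing in them shows that a center difference would shrink over time. If it is stable at an assumed 0.3 to 0.5 SD, with ρ at 0.6 to 0.7, ANCOVA gives about 10% to 28% false positives, against about 38% to 79% for Mann-Whitney. No choice among these tests separates center from intervention when each arm is one center.

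**What to change.** Rewrite the Data analysis paragraph as follows.

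- **Main analysis.** For every outcome, whatever the normality result, compare the groups at both follow-ups with the baseline score as covariate. Use ANCOVA at each follow-up, or a mixed model with group, time and group-by-time. Say explicitly that the three-month survey is included.
- **Non-normality.** Judge it on model residuals. If they are clearly non-normal, keep the baseline adjustment and use rank ANCOVA or bootstrap intervals.
- **Within-group comparisons.** Replace Kruskal-Wallis with Friedman and label the results descriptive.
- **Linkage.** State how one person's three surveys are linked, for example by a self-generated code. Data collection and instruments says they are posted anonymously, and every paired or adjusted analysis depends on linkage.
- **Limitation.** State that adjustment reduces but does not remove bias from a stable center difference, and does not resolve the one-center-per-arm design.

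The cost is one rewritten paragraph and a little more analysis work. No extra measurements are needed beyond a linking code, if none is planned.

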## Discussion

The present study will be the first attempt to examine the effectiveness of an educational intervention, developed based on the SCT and integrated into the PRECEDE-PROCEED model, in improving resilience, social capital, PWB, and HPL among HCW. The ultimate goal of the study is present a workplace intervention that will boost resilience, social capital, PWB, and HPL for the benefit of employees and employers. This evidence-based study has several strengths, as we discuss below.

The extant literature includes several intervention studies to improve workplace health. Nevertheless, there are contradictory results. Whilst some interventions have confirmed the effectiveness of resilience training [43], other studies have considered it to be insignificant. The lack of consensus may be due to the quality of the intervention program, or the study settings or the statistical population involved in the study, or the measures used, or a combination of all of these. Workplace interventions to improve employee health and quality of life are complex. There is a need to use established theories and principles, as well as a health promotion/illness-prevention framework to support the essential risk assessment process [68], yet the literature suggests this is not so. This study is a theory-based intervention based on an established health promotion framework, using delivered using theory-based educational practices. This is a strength of this study.

This study will be an RCT—the most powerful tool in experimental research to investigate the effectiveness of an intervention [69, 70]. Conducting a randomized interventional study accordingly makes it possible to examine the effects of the intervention on the outcomes among individuals in experimental and control groups [71].

Another strength of this study is that the contents of the educational sessions will be delivered to the participants face-to-face [53] and using a variety of activities and media to support assimilation of the knowledge materials both during the sessions and as homework. This can help increase the learning of more contents during the education process [59, 60].

The educational sessions have as their focuses the main concepts found to influence employee health in the modern workplace. The ten sessions include educational practices to boost resilience skills, and to adopt healthy behaviors. The primary aim is to support HCW who need to be mentally resilient and flexible so that they can provide good services to others in society [72]. Resilience is one of the effective factors in employee performance [73]. Ultimately, the study results will have implications in practice for promoting resilient behaviors in HCW. Then, assuming this intervention is found to be effective in this group of employees, it can be put to the test in other organizations and on their employees. Certainly, there is a business case for intervention, and interventions in the workplace support public health, and mental health agendas [68]. Thus, a focus on HCW when designing novel, expensive interventions to improve quality of life in the working population is an effective approach.

A potential limitation of this study is that it was not possible to run a small pilot of the educational program in advance of the full RCT. This, however, is typical of comprehensive intervention studies that use RCT with a longitudinal element to assess sustainability of the learning. Members of the research team have experience of educational interventions in other context, and our preparatory work indicated that the intervention is feasible. Similarly, it is unlikely that we will be able to separate out the different needs for the difference types of HCW in this study. A challenge with pilot studies for complex projects, and for accounting for all job roles are threefold: resource costs, time, and sufficiency of participants. We are confident, however, that we will have enough of all three to meet the aim and objectives of the project.

## Conclusion

The present study describes a protocol for an RCT to evaluate the effectiveness of an intervention based on the SCT using the PRECEDE-PROCEED health promotion model to boost resilience, social capital, PWB, and HPL among the HCW in the city of Shiraz, Iran. The methodology is robust. The results will provide information about the effectiveness of theory-based interventions on promoting resilient behaviors and the potential of these interventions to influence outcomes, such as social capital, PWB, and HPL in future research.

## Data Availability

Not applicable. The manuscript does not report data. The datasets subsequently generated and/or analyzed during the current study may be made publicly available following conclusion of ongoing research. Requests for data may be made at any time to the corresponding author.

## Abbreviations

HCW: Healthcare workers
SCT: Social cognitive theory
PWB: Psychological wellbeing
QoL: Quality of life
HPL: Health-promoting lifestyle
CONSORT: Consolidated standards of reporting trials
RCT: Randomized controlled trial
